## 6. Sample size estimates

The study hypothesized that there is no difference in 90-day risk of stroke (ischemic or hemorrhagic) in those treated with a 3-month regimen of ticagrelor initiated with a loading dose of 180 mg followed by 90 mg bid compared with a 3-month regimen of clopidogrel initiated with a loading dose of 300 mg followed by 75 mg/d when therapy is initiated within 24 hours of symptom onset in patients with TIA or minor ischemic

stroke carried *CYP2C19* LOF allele treated with aspirin 75 mg/d.

The minimum necessary sample size in the trial is established by the requirement to detect the smallest expected, clinically meaningful treatment difference comparing the treatment with placebo. Based on the genetic sub-analysis of the CHANCE study, we presume that the 90-day risk of stroke recurrence in *CYP2C19* loss-of-function allele carriers is about 9.4%, and 6.7% for noncarriers. With the point-of-care identification of the *CYP2C19* loss-of-function allele carriers to assess a proper pharmacogenetic approach for patients with high-risk TIA or MIS, we assumed a 25% relative risk reduction with alteration from clopidogrel to ticagrelor (90-day risk of stroke recurrence: 7.1%). Considering the potential impact of the interim analyses on the probability of type I error, we adjusted the statistical significance to a 2-sided  $\alpha$  of 0.048. With a sample size of 6,396 patients, we will have 90% power to detect a relative risk reduction (Ticagrelor: loading dose: 180mg, 90mg bid on day 2-90 vs. Clopidogrel: loading dose: 300mg, 75mg qd on day 2-90) of 25% and 5% dropouts (medication nonadherence). Assuming 58.8% prevalence of *CYP2C19* loss-of-function allele carriers in a Chinese population, we projected screening 10,878 patients would be necessary. Based on the results of interim analysis, the DSMB will recommend whether the sample size need to be re-calculated.

According to the DSMB meeting on April 7, 2021, the DSMB lookup the overall event rates of the trial and suggested not to unblind the treatment assignment in the interim analysis. Therefore, comparison of efficacy and safety outcome between two treatment groups were not performed in the interim analysis, and sample size was not re-calculated. The type I error level of the statistical significance will be set to a 2-sided  $\alpha$  of 0.05 in the final analysis.

## **7. Analysis populations**

### **Full Analysis Set (FAS):**

According to the basic principle of intention-to-treat (ITT), all patients who were enrolled, randomized and had the record of at least one-day treatment of study drugs will be included. Subjects missing outcome data will be censored at the last follow-up assessment time (end of study or last visit preceding loss to follow up). This population will be the primary population for analyses of efficacy.

### **Per Protocol Set (PPS)**

Per Protocol Set (PPS) is a subset of FAS. All patients with finishing the treatment without violating the trial program seriously are included in PPS. The exact definition of a serious violation will be finalized at the time of data review and may generally include (but is not limited to) the following criteria: failure to meet the main inclusion criteria, concomitant treatment that seriously interferes with the evaluation of the efficacy of study drugs after randomization, poor compliance, and exceed the time window of follow-up seriously and so on. A partial protocol violator will be included in the Per Protocol Population up to the time of their violation. For the Per Protocol Population, participants will be analyzed according to the treatment received, providing the same treatment was taken for the duration of the study. If study medication was changed then the participant will be considered a partial protocol violator (from the point of change onwards).

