### **13.3.1 Analysis sets**

**Full analysis set (FAS):** FAS is the set for efficacy evaluation. All efficacy variables will be analyzed using the FAS. According to the ITT principle, the FAS includes

patients who are enrolled, randomized and have the record of at least one-day treatment of study drugs. Subjects with missing outcome data will be censored at the last follow-up assessment time (end of study or last visit preceding loss to follow up).

**Per Protocol set (PPS):** PPS includes subjects who completed study treatment without serious violation against protocol. Definition of serious violation against protocol will be confirmed at data review. Generally, it may include the following situations (but not limited to these situations): failure to meet the main inclusion criteria, concomitant treatment that seriously interferes with the evaluation of the efficacy of study drugs after randomization, poor compliance, and follow-up beyond the time window. PPS is the secondary analysis population for efficacy evaluation, ~~but~~ if its results are inconsistent with the full analysis set, detailed analysis of the inconsistent results is required.

**Safety analysis set (SS):** SS includes all patients who received at least 1 time of study drugs and safety assessment. Throughout the safety results sections, erroneously treated patients (eg, those are randomized to ticagrelor and aspirin group but are actually given clopidogrel and aspirin) will be accounted for in the actual treatment group.

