### **3. Study Endpoint(s)**

#### **Primary Efficacy Endpoints:**

Any new stroke events (ischemic stroke or hemorrhagic stroke) within 3 months.

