### Protocol Deviations

Subject data will be examined for evidence of protocol violators in order to assess how well the protocol was followed. Inclusion and exclusion criteria are detailed in the study protocol.

Subjects who commit protocol violations will be included in the FAS Population but excluded from the Per Protocol Population. These protocol violations will be shown in a listing. Subjects can either be full or partial protocol violators. A full protocol violator is completely excluded from the Per Protocol Population. A partial protocol violator has only some data excluded. For subjects who violated the protocol during the treatment period due to unpermitted changes in the medication or prohibited concurrent medication, the analysis will only use data recorded prior to the violation. For all violations which reference the treatment period, the treatment start date will be used as the reference date.

A listing of all possible protocol violators will be produced for clinical review. The final list of subjects who are protocol violators and are therefore excluded from the Per-Protocol population will be agreed by the study team.

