## **12.Efficacy Analyses**

### **Primary Efficacy Analysis**

The primary endpoint is the rate of new stroke (both ischemic and hemorrhagic) reported during the 3 months treatment period. FAS will be the primary population for efficacy analyses. PPS will be used as secondary population for the efficacy analyses. If the results in the PPS population are inconsistent with the FAS population, detailed analysis of the inconsistent results is required.

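### The per-protocol set requires finished treatment and does not say that a stroke or death counts as finishing, so some patients leave it together with their primary event

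*Supplement*

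**What the plan says.** The two current documents agree on who belongs to the PPS. SAP v1.3, section 7 (Per Protocol Set): "All patients with finishing the treatment without violating the trial program seriously are included in PPS". Protocol v1.4, section 13.3.1: "PPS includes subjects who completed study treatment without serious violation against protocol". Finishing treatment and having no serious violation are two separate conditions. Finishing is not defined for a patient who has an outcome event or dies.

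The SAP adds a second route into the set. Section 7 continues: "A partial protocol violator will be included in the Per Protocol Population up to the time of their violation". It then makes a patient whose study medication was changed a partial violator from that moment on. Section 11 (Protocol Deviations) says "A partial protocol violator has only some data excluded". It ties the use of data from before the violation to medication changes that were not permitted and to prohibited concomitant drugs.

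On the role of the set, SAP section 12 states "PPS will be used as secondary population for the efficacy analyses", and then: "If the results in the PPS population are inconsistent with the FAS population, detailed analysis of the inconsistent results is required". The primary endpoint is "Any new stroke events (ischemic stroke or hemorrhagic stroke) within 3 months".

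**The concern.** Finishing three months of treatment is a condition met or failed after randomisation, and the outcome itself can decide which. A patient who takes every tablet and dies of a stroke on day 10 has broken no rule, yet cannot finish. The same holds for a patient whose study drug is permanently stopped, as the protocol allows, after a stroke or haemorrhage. On the text neither is a finisher and neither is a violator, so each drops out of the PPS together with the stroke that the analysis is meant to count. A patient who took a prohibited drug on day 10 contributes data up to that day.

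What is at stake is the efficacy analysis that the SAP sets beside the primary one. A set chosen partly by outcome can create a disagreement with the full analysis set (FAS), or conceal one, for reasons unrelated to adherence. The SAP obliges the team to explain any such disagreement.

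**Working it through.** **1. Does the protocol let an event end treatment by a permitted route?** Protocol v1.4:

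- Section 7.6.1 lists severe GUSTO bleeding as a reason for temporary interruption. Appendix Table 6 counts primary intracranial haemorrhage as severe bleeding. Restart depends on the investigator judging that the drug was unlikely to be the cause.
- Section 7.6.2 permits a permanent stop for an adverse event that makes continuation too risky, for a clear anticoagulation indication, or when the investigator decides against restarting.
- Section 11.5.3 has study drug interrupted or withdrawn when an adverse event occurs. Section 11.2.1 counts worsening of the qualifying event as an adverse event.
- Section 7.6.3 puts patients who stop permanently on conventional therapy.

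None of these is a violation. Death before day 90 always prevents completion.

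**2. Does the partial-violator rule bring these patients back?** Not clearly. Section 11 of the SAP confines the retained data to unpermitted changes and prohibited drugs, and a permitted stop or a death is neither. Whether a permitted stop followed by conventional therapy means that medication was changed, in the sense of section 7, is not stated. Where a prohibited drug is given after a stroke, the patient can be read as a partial violator from that point, and the earlier stroke stays. Whether an event counts can then depend on what was prescribed after it.

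**3. Expected events, after reproducing the plan's sample size.** Inputs from SAP section 6: risks 9.4% and 7.1%, two-sided alpha 0.048, power 90%, dropout 5%. Allocation is 1:1 (protocol section 6.2).

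n per arm = [z(1−α/2)·√(2·p̄·q̄) + z(0.90)·√(p0·q0 + p1·q1)]² / (p0 − p1)², with p̄ = 0.0825

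= (1.977 × 0.3891 + 1.282 × 0.3887)² / 0.023², which rounds up to 3,038 per arm, or 6,076 in total.

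6,076 / 0.95 = 6,396, the plan's figure.

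Expected events with 3,198 per arm: 3,198 × 0.094 = 301 and 3,198 × 0.071 = 227, together 528. Risk ratio = 7.1 / 9.4 = 0.755.

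**4. Effect of removing event patients.** If a share f of the e event patients in an arm of n leaves the PPS, the remaining risk is e(1 − f) / (n − e·f). The documents give no value of f, so those below are assumptions. Only event patients are removed, and none returns through the partial-violator route. Power is for two proportions at two-sided 0.05.

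| Removed, clopidogrel / ticagrelor | Events left | Risk, clopidogrel | Risk, ticagrelor | Risk ratio | Power |
|---|---|---|---|---|---|
| 0% / 0% | 528 | 9.40% | 7.10% | 0.755 | 0.917 |
| 10% / 10% | 475 | 8.54% | 6.44% | 0.754 | 0.890 |
| 25% / 25% | 396 | 7.22% | 5.42% | 0.751 | 0.833 |
| 50% / 50% | 264 | 4.93% | 3.68% | 0.746 | 0.675 |
| 10% / 20% | 452 | 8.54% | 5.76% | 0.675 | n/a |
| 20% / 10% | 445 | 7.66% | 6.44% | 0.840 | n/a |

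Equal removal leaves the ratio near 0.75 and costs events and power. A 10-point difference between arms moves it to 0.675 or 0.840, depending on direction.

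**The case against.** The best defence is that the rule need not be read so strictly. The SAP says that finishers without serious violation are included, and then admits others as partial violators. A stroke that precedes a medication change or a prohibited treatment can stay in. A reader might infer that every stroke patient who comes off drug is lost. The documents do not support that. No passage names stroke as a reason to stop study drug, protocol section 7.6 makes permanent stopping a last resort, and severe bleeding leads first to a temporary stop. Event-free patients who stop early or comply poorly can also be excluded, so the exclusions are not confined to patients with events.

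A reader might also infer that harm could be concealed. It could not be by this rule. Safety is analysed in the Safety Set, where bleeding and deaths are compared without a completion condition. The primary efficacy analysis uses the FAS, which has none either.

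Finally, the ratio shifts only if removal differs by arm, and the documents do not show that it will in a double-blind trial. Section XI of the protocol lists haemorrhagic stroke as a side effect of ticagrelor and not of clopidogrel. That makes a difference conceivable but gives no size.

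These points limit the concern. They do not remove it, because deaths and permitted stops after an event remain outside both routes on the text.

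**Conclusion.** The point holds within limits. As written in both documents, the PPS excludes patients who die before day 90. It also excludes those who permanently stop by a permitted decision after a stroke or haemorrhage, unless that stop is treated as a medication change. Their primary events go with them. Other post-stroke events may be kept through the partial-violator and change-of-medication sentences.

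The effect is confined to the secondary efficacy analysis. If removal is equal in the two arms, the loss is in events and power. If it differs, the risk ratio is distorted in either direction, as the 0.675 and 0.840 illustrations show against 0.755. Those figures rest on the planned event rates, on assumed shares, and on simple 90-day risks in place of the Cox model. A reader might want a count of events that will be lost. The documents contain no stopping rate from which to derive one.

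**What to change.** In SAP section 7 and protocol section 13.3.1, replace the completion condition. Judge completion and adherence only up to the earliest of first primary event, death or day 90. A patient who was adherent and without serious violation until then belongs to the PPS, with the event counted.

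Reconcile this with the partial-violator rule in SAP sections 7 and 11. State whether a permitted permanent stop counts as a change of medication, and up to what time such a patient contributes. If event-free patients are to be censored when they stop, say so, and acknowledge that this censoring may be informative.

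The cost is an amendment to the wording of both documents before unblinding. Sample size, visits, data collection and patient management do not change.

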### **Safety Set (SS)**

All patients who received at least 1-time of study drug according to the study protocol and safety assessment available will be included in the safety population. Throughout

the safety results sections, erroneously treated patients (eg, those randomized to ticagrelor and aspirin group but actually given clopidogrel and aspirin) will be accounted for in the actual treatment group. This population will be used for safety analyses.

## 8. Treatment comparisons

The treatment comparison of interest in this study is to assess the antiplatelet effects of ticagrelor plus aspirin versus clopidogrel plus aspirin in Chinese patients in *CYP2C19* LOF alleles carriers with TIA or minor stroke.

## 9. General considerations for data analyses

All programming will be performed using SAS Version 9.4. All analysis output will use the following treatment group naming conventions and treatment order:

**Ticagrelor plus aspirin group:** Ticagrelor of loading dosing of 180mg followed by 90mg bid for 3 months plus aspirin of loading dose of 75-300mg followed by 75mg daily for 21 days.

**Clopidogrel plus aspirin group:** Clopidogrel of loading dosing of 300mg followed by 75mg daily for 3 months plus aspirin loading dose of 75-300mg followed by 75mg daily for 21 days.

All statistics were two sided with a  $P < 0.05$  considered significant.

### Multicenter Studies

As stated in the protocol, centers with less than 20 subjects will be pooled with larger centers within the same geographic region so that centers are of a reasonable size for the purpose of the statistical analyses. This process will be performed and finalized before the treatment codes are unblinded.

In multicenter randomized controlled clinical study, there were some difference effect in different center due to different baseline, clinical practice or other factor, therefore, central effect analysis was required. Stratified analysis was used to exclude the mixed effect of results caused by center effect: each center was served as a stratum, calculating the HR by Cox proportional hazards model.

### Examination of Subgroups

The rate of new stroke (ischemic or hemorrhagic) at 90 days will be presented for each level of the covariates listed below. The extent to which the treatment effect varies across levels of each subgroup will be assessed through interaction tests.

### Multiple Comparisons and Multiplicity

A single primary efficacy variable has been defined for this study, with all other efficacy variables identified as secondary or other. Similarly, only one treatment comparison is of interest in the study and therefore there are no requirements to adjust for multiple comparisons or multiple endpoints within this study.

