#### 2. Efficacy analysis

- 1) Primary efficacy endpoint:

Kaplan-Meier estimates of the cumulative risk of new stroke within 3 months will be reported. The hazard ratio with 95%CI for the treatment comparison will be derived using a Cox's proportional hazards model. The log-rank test will be used to evaluate the statistical significance of the treatment effect.

2) Secondary efficacy endpoint:

- ① Kaplan-Meier estimates of the cumulative risk of stroke or combined vascular events within 3 months will be reported. The hazard ratio with 95%CI for the treatment comparison will be derived using a Cox's proportional hazards model. The log-rank test will be used to evaluate the statistical significance of the treatment effect;
- ② ORs and 95%CIs will be compared using  $\chi^2$  test or logistic analysis;
- ③ Continuous variables will be compared using t-test or Wilcoxon sum rank test.
- ④ Categorical variables will be compared using a  $\chi^2$  test, Fisher exact test, or Wilcoxon rank sum test as appropriate;
- ⑤ Comparison of neurologic deficits scales and EQ-5D-5L scales will be performed using non-parametric analysis;
- ⑥ Extreme values will be thoroughly checked and corrected before analysis, sensitivity tests will be prespecified;

All statistics will be 2-sided with  $P < 0.05$  considered significant.

3) Subgroup analyses:

The primary efficacy endpoint will also be analyzed stratified by age (<65 vs.  $\geq$  65 years), gender (men vs. women), Body Mass Index (BMI), index event type (TIA vs. minor stroke), time from index event to randomization, etiology subtype, diabetes mellitus, hypertension, type of LOF allele, previous ischemic stroke or TIA, prior

antiplatelet therapy, prior statin therapy, and prior smoking status. Symptomatic intracranial and extracranial artery stenosis will also be evaluated in subgroup analyses.

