#### **Secondary Efficacy Endpoint:**

- 1) Any new stroke events (ischemic stroke or hemorrhagic stroke) within 30 days and 1 year;
- 2) New clinical vascular events (ischemic stroke/ hemorrhagic stroke/ TIA/ MI/ vascular death) within the 3 months and 1 year;
- 3) New ischemic stroke within 3 months and 1 year;
- 4) Disabling stroke (Modified Rankin Scale score, mRS>1) at 3 months and 1 year;
- 5) Incidence and severity of recurrent stroke and TIA during follow-up to 3 months and

1-year (Severity is measured using a six-level ordered categorical scale that incorporates the mRS: fatal stroke/severe non-fatal stroke [mRS 4 or 5]/moderate stroke [mRS 2 or 3]/mild stroke [mRS 0 or 1])/TIA/no stroke-TIA);

6) Neurological impairment at 3 months (NIHSS increased  $\geq 4$  from baseline);

7) Quality of Life (EuroQol EQ-5D scale) at 3 months and at 1 year.

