**Rate of new ischemic stroke within 3 months**

The rate of ischemic stroke occurring within 3 months will be analyzed using a Cox proportional hazard model, with the pooled study center as a random effect. This will also be presented graphically on a Kaplan-Meier curve. The hazard ratio with 95% CI will be reported. The log-rank test will be used to evaluate the statistical significance of the treatment effect.

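### The SAP waives adjustment for multiple endpoints but applies two-sided P<0.05 to 13 secondary efficacy analyses, with no gate on the primary, testing order or exploratory label

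*Supplement*

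**What the plan says.** SAP v1.3, section 9 (Multiple Comparisons and Multiplicity), starts from this premise: "A single primary efficacy variable has been defined for this study, with all other efficacy variables identified as secondary or other". It adds that only one treatment comparison is of interest, and concludes that "there are no requirements to adjust for multiple comparisons or multiple endpoints within this study".

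The opening of the same section sets one rule for everything: "All statistics were two sided with a $P < 0.05$ considered significant". Protocol v1.4, section 13.3.2, has an equivalent line ("All statistics will be 2-sided with" the same 0.05 threshold) directly after its list of secondary endpoint methods.

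SAP section 3 lists seven secondary efficacy endpoints, most at two time points, for example "Any new stroke events (ischemic stroke or hemorrhagic stroke) within 30 days and 1 year". Section 12 gives each its own analysis. The six time-to-event paragraphs all end with the sentence that also closes the primary analysis: "The log-rank test will be used to evaluate the statistical significance of the treatment effect".

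Protocol v1.4, section 13.3, leaves the definition of all planned analyses to the SAP, so no other document is expected to supply a rule for secondary claims.

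**The concern.** A single primary comparison needs no multiplicity adjustment. The SAP extends that argument to every endpoint in the study, which does not follow unless the other endpoints support no significance claims. The plan does not say that. It sets a significance threshold for every statistic, and for six secondary endpoints it names significance as the purpose of the test.

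Followed as written, the plan would allow a secondary result with P<0.05 to be declared a significant treatment effect even if the primary test failed. Stroke at 30 days, stroke at 1 year, ischemic stroke and the vascular composite all overlap heavily with the primary endpoint (any new stroke within 3 months). A chance finding on one of them could therefore easily be read as confirmation. What is at stake is what the trial may conclude from its secondary endpoints.

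**Working it through.** **1. What the plan's own figures control.** The documents give no family-wise error figure for the secondary endpoints. The one design figure that can be reproduced concerns the primary alone. Inputs from SAP section 6: 9.4% versus 7.1%, two-sided alpha 0.048, power 90%, 5% dropout. The mean risk is 0.0825.

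n per arm = [1.977·√(2·0.0825·0.9175) + 1.282·√(0.094·0.906 + 0.071·0.929)]² / 0.023² = 3,038

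The total is 6,076, and 6,076/0.95 = 6,396, as stated. Sample size and alpha are built on the primary comparison only.

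**2. Count of secondary efficacy analyses** (SAP v1.3, sections 3 and 12).

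| Endpoint | Time points | Analyses | Named test |
|---|---|---|---|
| Any new stroke | 30 days, 1 year | 2 | log-rank |
| Vascular composite | 3 months, 1 year | 2 | log-rank |
| Ischemic stroke | 3 months, 1 year | 2 | log-rank |
| Six-level severity | 3 months, 1 year | 2 | Wilcoxon, p value reported |
| EQ-5D | 3 months, 1 year | 2 | t-test or Wilcoxon |
| Disabling stroke | 3 months, 1 year | 2 | none: odds ratio, 95% CI |
| NIHSS worsening | 3 months | 1 | none: odds ratio, 95% CI |

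The total is 13. Ten name a test (6 + 2 + 2). The other three come under P<0.05 only through the general rule in section 9. Subgroup and safety comparisons are not counted.

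**3. Independent tests, no true effect on any secondary endpoint.**

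- Either direction, 13 analyses: 1 − 0.95¹³ = 0.487. Expected false positives: 13 × 0.05 = 0.65.
- False benefit of ticagrelor (one tail, 0.025 each): 1 − 0.975¹³ = 0.280.
- Only the 10 analyses with a named test: 1 − 0.95¹⁰ = 0.401 in either direction, and 1 − 0.975¹⁰ = 0.224 for a false benefit.

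**4. Correlated tests.** The endpoints overlap, so independence gives an upper reference. With a common correlation ρ between test statistics and c = 1.96:

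- Either direction: 1 − ∫ [Φ((c − √ρ·u)/√(1−ρ)) − Φ((−c − √ρ·u)/√(1−ρ))]¹³ φ(u) du
- False benefit: the same integral without the second Φ term.

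| Assumed ρ | Either direction | False benefit |
|---|---|---|
| 0 | 0.487 | 0.280 |
| 0.3 | 0.418 | 0.214 |
| 0.5 | 0.334 | 0.167 |
| 0.7 | 0.241 | 0.120 |
| 0.9 | 0.138 | 0.069 |

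**5. Simulation check.** Patients were simulated under the null: 3,198 per arm, 13 nested endpoints, 3,000 replicates, and three assumed sets of event rates and overlap. Simple normal tests stood in for the planned ones.

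| Mean correlation between statistics | Either direction | False benefit |
|---|---|---|
| 0.39 | 0.31 | 0.16 |
| 0.54 | 0.29 | 0.15 |
| 0.67 | 0.24 | 0.11 |

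These results agree with the range in step 4.

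**The case against.** The strongest reply is that the SAP already ranks its endpoints. It names one primary variable, and the formal hypothesis, the sample size and the final alpha all concern that variable alone. No passage defines trial success by a secondary endpoint or lets one replace a failed primary. The P<0.05 line can be read as a generic convention for labelling p values. Multiplicity was considered openly, in a section of its own. On this view the point is about later reporting and not about an analysis rule.

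Much of this stands. The primary inference is sound, and no estimate or confidence interval would change. It does not settle the matter, because the word secondary alone does not make a test descriptive when the plan states a threshold for all statistics and gives six secondary tests the same stated purpose as the primary.

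Three stronger readings are tempting, and the documents do not support them:

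- **A 1 in 3 chance of a false secondary benefit.** One in 3 (0.334) counts false results in both directions at an assumed correlation of 0.5. A false benefit uses one tail: 0.167 at that correlation, and no more than 0.280 even if the tests are independent.
- **Thirteen significance tests.** Three of the 13 analyses specify only an odds ratio with its interval.
- **Inflated error for the trial's main conclusion.** The single primary test is unaffected.

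**Conclusion.** The concern holds for claims drawn from the secondary efficacy endpoints, and only for those. The SAP's waiver is valid for the primary comparison. Applied to multiple endpoints alongside a blanket 0.05 rule, it leaves secondary significance claims without error control.

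The size depends on correlations that the documents do not give. Over the assumed range of 0 to 0.9, a false significant result in either direction has a probability between 0.49 and 0.14, and a false benefit of ticagrelor between 0.28 and 0.07. Even at 0.9 both are about 2.8 times the per-test level (0.138/0.05 and 0.069/0.025). All figures assume no true effect on any secondary endpoint and count all 13 analyses under the general rule. The point is worth acting on because the wording decides what the trial may claim and is cheap to change.

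**What to change.** In SAP section 9, replace the last sentence of Multiple Comparisons and Multiplicity with text to this effect:

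> Only the primary comparison is tested, at two-sided 0.05. Secondary efficacy endpoints are exploratory. They are reported as effect estimates with 95% confidence intervals not adjusted for multiplicity, and no statistical significance will be claimed for them.

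Then limit the general P<0.05 rule at the start of section 9 to the primary comparison, and delete the sentence "The log-rank test will be used to evaluate the statistical significance of the treatment effect" from the secondary paragraphs of section 12, or reword it so that it no longer speaks of significance. Protocol v1.4, section 13.3.2, carries the same general rule, so the SAP should say that its own statement governs.

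If the sponsor wants confirmatory secondary claims, an optional alternative is a short fixed sequence at 0.05, tested only after a significant primary, with everything after the first non-significant result exploratory. This is the sponsor's choice and not a required change.

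The cost is wording only, with no extra data or patients. SAP section 6 records that treatment groups were not compared at the interim, so at v1.3 the text could still be settled before unblinding. The downside is that the sponsor gives up significance claims on secondary endpoints, or restricts them to the ordered few.
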